## Abstract

Research on the use of Acceptance and Commitment Therapy (ACT) for patients with degenerative lumbar pathology awaiting surgery are limited. However, there is evidence to suggest that this psychological therapy may be effective in improving pain interference, anxiety, depression, and quality of life. This is the protocol for a randomized controlled trial (RCT) to evaluate the effectiveness of ACT compared to treatment as usual (TAU) for people with degenerative lumbar pathology who are candidates for surgery in the short term. A total of 102 patients with degenerative lumbar spine pathology will be randomly assigned to TAU (control group) or ACT + TAU (intervention group). Participants will be assessed after treatment and at 3-, 6-, and 12-month follow-ups. The primary outcome will be the mean change from baseline on the Brief Pain Inventory (pain interference). Secondary outcomes will include changes in pain intensity, anxiety, depression, pain catastrophizing, fear of movement, quality of life, disability due to low back pain (LBP), pain acceptance, and psychological inflexibility. Linear mixed models will be used to analyze the data. Additionally, effect sizes and number needed to treat (NNT) will be calculated. We posit that ACT may be used to help patients cope with the stress and uncertainty associated with their condition and the surgery itself.

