### 2.2. Participants and Sample Size

The sample size was estimated through R with R Studio using the package “pwr.t.test” version 4.3.0. This sample size was determined to achieve a power of 80%, a significance level of 5%, and a treatment effect size based on Cohen’s *d* of 0.64 and 0.73 for pain interference (BDI) at post-treatment and at follow-up, respectively [48]. Considering a dropout rate of 30% [48,49,50,51], it will be necessary to include 51 subjects in each study arm. A total of 102 patients with degenerative lumbar pathology who are candidates for lumbar surgery from the Spine Unit of Hospital del Mar (Barcelona, Spain) will be recruited for this study.

Patients who have been scheduled for surgery in the Spine Unit and who have been diagnosed with degenerative pathology that also present psychosocial risk factors for CPSP, as determined by screening questionnaires, will be assessed by the Pain Unit psychiatrist starting June 2023 and will be recruited if they meet the selection criteria. Inclusion criteria will be (a) age 18–80 years, (b) adequate understanding of Spanish or Catalan, (c) meeting the diagnostic criteria for the LBP/degenerative low back pathology that indicates a candidate for first surgical treatment according to the clinical history (International Classification of Diseases [ICD]-10 codes for surgical and diagnostic processes) [52], (d) presence of psychosocial risk factors for CPSP, (e) having an internet connection on a smartphone, tablet, or computer to be able to participate in online therapy, and (f) giving authorization by signing informed consent. Specifically, the psychosocial risk factors associated with CPSP are anxiety, depression, catastrophizing, and fear of movement [35,36]. During the outpatient visit to the Spine Unit, and once the surgical intervention has been proposed and accepted by the patient, the patient will complete three self-administered questionnaires: The Hospital Anxiety and Depression Scale (HADS), Pain Catastrophism Scale (PCS), and Tampa Scale of Kinesiophobia (TSK-11). To select the participants, the cut-off points are high in relation to the HADS (cut-off point ≥ 11), PCS (cut-off point ≥ 24), and TSK-11 (cut-off point ≥ 27), which are based on what was suggested by the authors and reviewers of the adaptations of each questionnaire [53,54,55].

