##### Primary Outcome Measure

The Brief Pain Inventory (BPI) [63,64] is a self-report measure that assesses chronic pain in a multidimensional way. It provides information on pain interference (primary outcome) and pain intensity (secondary outcome) with patients’ daily functioning and activities. An abbreviated version of 11 items is available. The first 4 items evaluate the pain intensity in the last 24 h, ranging from 0 (no pain) to 10 (the worst pain imaginable). Subsequently, 7 items (i.e., general activity, mood, ability to walk, ability to work including domestic work, relationships with other people, sleep, and ability to enjoy the life) are assessed from 0 (does not disturb) to 10 (totally disturbs) to report the degree of involvement of chronic pain in these areas of the person’s functioning. The higher the score in the areas of the questionnaire, the greater the intensity of perceived pain, as well as the greater degree of involvement of chronic pain in the functioning of the person in the various areas explored.

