### 2.6. Statistical Analysis

Data analyses will be carried out using the statistical packages SPSS v26.0, R with R Studio v4.0.2, and MPlus v7.4. Comparative analyses of continuous data will be performed using the Student’s *t* test or their non-parametric equivalents (i.e., Mann–Whitney U or Kruskal–Wallis test), depending on the characteristics inherent to the variables under study. The Chi-Square test or Fisher’s exact test will be used, as appropriate, for categorical variables. The Bonferroni correction will be applied in all post hoc tests. In all statistical tests performed with the outcome variables, a statistical significance level of 0.05 will be used. In adherence with CONSORT recommendations, potential baseline differences in sociodemographic and clinical characteristics are considered irrelevant after randomization and, as a result, were not included as covariates in the analyses of RCT outcomes.

The main analysis will compare the effect ACT compared to TAU on the primary outcome (pain intensity and pain interference at 12-month follow-ups). All data analyses will be carried out following an intention-to-treat (ITT) principle, that is, regardless of protocol adherence. Then, we will compute analysis of the primary outcome post-treatment and analysis of the secondary and treatment process outcomes at post-treatment and at 12-month follow-up. The analyses will be replicated from a per-protocol approach. Multi-level, linear mixed models will be created using the restricted maximum likelihood method for the estimation of parameters. The effect sizes will be calculated according to Cohen’s *d*. A 5% significance level will be used in all 2-tailed tests, applying the Benjamini–Hochberg correction for multiple comparisons (to reduce the risk of false positives).

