It is hoped that ACT will improve the results in variables studied in relation to chronic pain in this population at high risk of postsurgical LBP. This study is justified because of the importance of identifying these psychosocial prognostic factors, and to be able to intervene with them, to improve the clinical outcomes of surgical treatment in patients with chronic degenerative LBP. The purpose is to apply ACT to improve these outcomes. Of the patients who are candidates for lumbar surgery, those with a high fear of movement (kinesiophobia), a high level of catastrophism, and the presence of anxiety and depression will be screened to focus the intervention on them. The ACT program has been designed to develop skills and tools with patients to enable them to regulate themselves in the face of pain, fear of movement, catastrophizing, anxiety, and depression. By applying this intervention, we will seek to improve pain acceptance and psychological flexibility with the idea of improving catastrophizing, kinesiophobia, anxiety, depression, quality of life, and overall personal functioning of people with chronic pain both before and after surgery, as measured by the degree of pain interference (primary endpoint of our study).

Predicting the prognosis in patients scheduled for surgery for LBP, through previous evaluation tests, could be efficient to apply them to complementary treatment modalities and thus prevent the chronification of pain and the worsening of functionality. People with chronic degenerative LBP who are candidates for surgery, with higher rates of catastrophizing, anxiety, depression, and fear of movement (kinesiophobia) will present a higher risk of chronic pain and a worse prognosis in relation to the efficacy of surgical treatment. We posit that participants receiving ACT will have greater improvement in pain intensity, pain interference, and quality of life, and less disability than participants receiving only TAU. It is hoped that ACT can improve the results in the variables studied in relation to chronic pain in this population with a high postsurgical risk of LBP.

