Sociodemographic and clinical questionnaire	X				
Primary outcome measure					
BPI (pain interference)	X	X	X	X	X
Secondary outcome measures					
BPI (pain intensity)	X	X	X	X	X
HADS (anxiety and depression)	X	X	X	X	X
PCS (pain catastrophizing)	X	X	X	X	X
PIPS (psychological inflexibility to pain)	X	X	X	X	X
TSK-11SV (fear of movement)	X	X	X	X	X
CPAQ-20 (pain acceptance)	X	X	X	X	X
SF-12 (health-related quality life)	X	X	X	X	X
OLBPDQ (functional status)	X	X	X	X	X

Note: BPI = Brief Pain Inventory-Interference Scale; HADS = Hospital Anxiety and Depression Scale; PCS = Pain Catastrophizing Scale; PIPS = Psychological Inflexibility in Pain Scale; TSK-11SV = Tampa Kinesiophobia Scale; CPAQ-20 = Chronic Pain Acceptance Questionnaire; SF-12 = Short-Form 12 Health Survey; OLBPDQ = Oswestry Low Back Pain Disability Scale.

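### Section 2.6 puts pain intensity into the 12-month primary outcome, although the protocol elsewhere makes pain interference the single primary outcome and intensity secondary

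*Protocol article*

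**What the plan says.** The sentence in section 2.6 (Statistical Analysis) that defines the main analysis reads: "The main analysis will compare the effect ACT compared to TAU on the primary outcome (pain intensity and pain interference at 12-month follow-ups".

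Other parts of the article say something different:

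- **Abstract:** "The primary outcome will be the mean change from baseline on the Brief Pain Inventory (pain interference", followed by "Secondary outcomes will include changes in pain intensity, anxiety, depression".
- **Introduction, objectives:** objective (a) labels interference as primary. Objective (b) lists intensity among the secondary outcomes.
- **Section 2.5.1, Primary Outcome Measure:** "It provides information on pain interference (primary outcome) and pain intensity (secondary outcome".
- **Table 2:** the row "BPI (pain intensity" stands under the secondary heading. Interference is the only row under the primary heading.
- **Section 3, Discussion:** "as measured by the degree of pain interference (primary endpoint of our study".
- **Section 2.2, sample size:** the effect sizes are "of 0.64 and 0.73 for pain interference (BDI) at post-treatment and at follow-up, respectively". None is given for intensity.

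The last paragraph of section 2.6 gives a third wording. It calls the primary outcome simply the BPI and defines responders by a one-point fall in the total BPI score, without naming a subscale.

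On multiplicity, section 2.6 sets a two-sided 5% level and a Benjamini–Hochberg correction for multiple comparisons. It does not say which tests form the family.

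**The concern.** The sentence that fixes the main analysis determines what the trial will conclude. It places two scores under one primary label. The article does not say whether they are co-primary, alternatives, or named together by mistake.

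An analyst who follows section 2.6 would test intensity as a primary endpoint. An analyst who follows the abstract, section 2.5.1 or Table 2 would not. If the two scores gave different answers, two people working from the same article could report opposite primary results. A benefit on intensity alone would count as primary success under one reading and as a secondary finding under the other.

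This is not a detail left out of a condensed article. The article states the primary outcome in two incompatible ways.

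**Working it through.** **1. The passages side by side**

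| Place | Interference | Intensity |
|---|---|---|
| Abstract | primary | secondary |
| Introduction, objectives (a) and (b) | primary | secondary |
| Section 2.5.1 | primary | secondary |
| Table 2 | primary | secondary |
| Discussion | primary endpoint | not named as primary |
| Section 2.2 (sizing) | d = 0.64 and 0.73 | no effect size |
| Section 2.6, main analysis | primary | primary |
| Section 2.6, responders | BPI total, no subscale named | BPI total, no subscale named |

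Section 2.6 also conflicts with itself. After the main-analysis sentence it separates the primary outcome at post-treatment from the secondary and process outcomes. Where intensity falls in that split depends on which definition is used.

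**2. What the sample size covers**

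Inputs from section 2.2: power 80%, significance level 5%, d = 0.64 or 0.73 for interference, dropout 30%, 51 per arm. Section 2.6 gives two-sided tests.

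- Normal approximation: n per arm = 2(1.960 + 0.842)² / d².
- d = 0.64: 2 × 7.85 / 0.4096 = 38.3, so 39. With the dropout allowance applied as a multiplier, 39 × 1.30 = 50.7, so 51. This reproduces the stated figure.
- d = 0.73: 2 × 7.85 / 0.5329 = 29.5, so 30, and 30 × 1.30 = 39. This does not give 51.

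The 51 per arm therefore follows from one comparison on interference at 5%, with no allowance for a second primary score. (Whether multiplying by 1.30 is the right way to allow for dropout is a separate matter.)

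**3. False-positive rate if either score counted**

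Assume no effect on either score and two two-sided z-tests with correlation ρ. The article gives no value for ρ.

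- Each tested at 0.05: P(any significant) = 1 − P(|Z₁| ≤ 1.96 and |Z₂| ≤ 1.96). At ρ = 0 this is 1 − 0.95² = 9.75%.
- Benjamini–Hochberg on exactly these two tests: a claim is made if the smaller p ≤ 0.025 or both p ≤ 0.05.

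| ρ (assumed) | Each at 0.05 | Benjamini–Hochberg on the pair |
|---|---|---|
| 0 | 9.75% | 5.0% |
| 0.5 | 9.1% | 4.8% |
| 0.7 | 8.3% | 4.6% |
| 0.8 | 7.8% | 4.4% |

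**4. What the correction cannot do**

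Assume interference truly does not change and intensity has d = 0.5, with 51 × 0.70 = 35.7 completers per arm. The mean of the intensity test statistic is 0.5 × √(35.7 / 2) = 2.11. With ρ = 0.5 and either score counting, a positive primary result appears in about 58% of trials at 0.05 each, and in about 46% under Benjamini–Hochberg on the pair. Nearly all of these are correct findings about intensity. They would still be reported as primary success although interference had not changed. The d of 0.5 is illustrative.

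**The case against.** The strongest reply is that the intended primary outcome is clear. Five other places agree on interference, all of them are published, and a later switch would be visible against them. Decision rules for several endpoints are also commonly left to the statistical analysis plan, which is not shown. Both points are fair, so the absence of an either-or-both rule is not raised as a fault here. But an analysis plan could only choose between the two statements. It would not make this sentence agree with the rest of the article.

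A reader might infer three stronger things that the article does not support:

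- **That the primary false-positive rate is close to 10%.** This ignores the Benjamini–Hochberg correction stated in the same paragraph. If it covers this pair, the rate stays at or below 5%. Because the family is not stated, neither figure can be taken as the trial's own error rate.
- **That the trial is badly underpowered because both scores must succeed.** Nothing in the article suggests such a rule, and any power figure for it needs an intensity effect and a correlation that the article does not give.
- **That intensity is foreign to what the therapy aims at, so that the two scores should be expected to diverge.** Section 2.4.1 stresses acceptance over control, but the discussion includes intensity in the study's aim and predicts greater improvement in it with ACT. The authors do expect an intensity benefit.

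The contradiction does not depend on any of these.

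**Conclusion.** Wrong as written. The main-analysis sentence in section 2.6 gives a definition of the primary outcome that the abstract, objectives, section 2.5.1, Table 2 and discussion contradict and that the sample size does not cover. The responder paragraph adds a third definition. No passage reconciles them. This conclusion rests on the text alone and needs no assumption.

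The size of the consequence is conditional. If either score could carry the primary claim, the false-positive rate lies between about 4.4% (correction applied to this pair, correlation 0.8) and 9.75% (no correction, independent scores). The correlations are assumed. Whichever end applies, the trial could be called positive on intensity alone, and controlling the false discovery rate does not say which score is primary.

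**What to change.** Three edits, all in section 2.6:

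1. Replace the main-analysis sentence with: *The main analysis will compare ACT + TAU with TAU on the primary outcome, BPI pain interference, at 12-month follow-up.*
2. List pain intensity with the secondary outcomes in the sentence on secondary and process outcomes.
3. In the responder paragraph, refer to the BPI interference score in place of the total score, and name interference as the primary outcome.

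No scoring rule for the interference items is proposed, because the article states none.

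The cost is a few words, with no new patients, measurements or procedures. The downside is that a benefit on intensity can be reported only as a secondary result, which is how Table 2 already classes it.

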## 3. Discussion

The present work describes the design and protocol of an RCT that aims to assess the effectiveness of ACT compared to TAU in patients with degenerative pathology of the lumbar spine who are candidates for surgery. The protocol for this RCT was designed using SPIRIT recommendations and registered in a clinical trial database (ClinicalTrials.gov, accessed on 5 December 2022) according to CONSORT guidelines. The interest is to explore the benefits of ACT applied before surgery in degenerative lumbar pathology to improve the results in pain and functionality in patients with a high risk of developing chronic pain.

Based on previous work from RCTs with ACT applied perioperatively in orthopedic and breast surgery [79,80], in which a decrease in pain interference and an improvement in anxiety levels were observed, we expect to be able to provide the scientific community with greater evidence of the usefulness of ACT perioperatively in relation to the pain interference in activities of daily living and the psychological variables explored in our study.

If the RCT findings are robust enough, ACT could be offered as an additional intervention to TAU, with a coherent strategic approach that is adjustable to the health resources allocated to patients who are candidates for lumbar surgery. In this RCT, in addition to evaluating the clinical effects of ACT in the short, medium, and long term, we will seek to recognize relevant moderators and mediators of clinical change. The possible withdrawal of patients from the trial will be one of the risk components that will be considered. In this sense, a sensitivity analysis will be developed as a strategy to determine the impact of adherence to the ACT protocol on the observed effects.

Within the process of community care and special programs of the Insititut de Neuropsiquiatria i Addiccions (INAD) of the PSMAR, there is a long tradition of care in the use of different group therapy programs in the adult population receiving inpatient and outpatient care. As part of this process, psychological group therapies are carried out in the hospital setting of the PSMar Pain Unit, which are aimed at improving coping with chronic pain by applying a therapeutic protocol based on ACT. We have adapted our ACT protocol that we use for patients with chronic pain to a pre-surgical protocol of 8 sessions in a group format, encompassing both a behavioral psychotherapeutic intervention and pain psychoeducation. Psychological intervention covers many key areas, including identifying personal functioning goals, observing, and describing physical pain and the difficult thoughts and feelings that come with pain, identifying avoidance behaviors and analyzing when they exacerbate pain, distress, anxiety, and dysfunction and noting the impact on pain of engaging in worthwhile activities gradually, with acceptance in mind.

Predicting prognosis in patients scheduled for surgery for LBP, by means of pre-assessment tests, could be efficient to apply in complementary treatment modalities, and thus prevent chronification of pain and worsening of functionality. Therefore, the objective of our study will be to test ACT in an RCT to better understand its impact in the short medium, and long term on the pain intensity, pain interference in activities of daily living, quality of life, mood, and pain disability. We will explore if applying ACT with an online preoperative program of 8 sessions, lasting 90 min, is effective, as well as analyzing patient adherence. We will investigate whether the results underscore and corroborate the possible benefits of integrating psychology services in multidisciplinary teams to prevent the incidence, intensity, and disability of CPSP. In our study, we will stratify the patients who have undergone ACT based on the number and type of psychological factors of CPSP presented, to see if there are significant differences.

It is hoped that ACT will improve the results in variables studied in relation to chronic pain in this population at high risk of postsurgical LBP. This study is justified because of the importance of identifying these psychosocial prognostic factors, and to be able to intervene with them, to improve the clinical outcomes of surgical treatment in patients with chronic degenerative LBP. The purpose is to apply ACT to improve these outcomes. Of the patients who are candidates for lumbar surgery, those with a high fear of movement (kinesiophobia), a high level of catastrophism, and the presence of anxiety and depression will be screened to focus the intervention on them. The ACT program has been designed to develop skills and tools with patients to enable them to regulate themselves in the face of pain, fear of movement, catastrophizing, anxiety, and depression. By applying this intervention, we will seek to improve pain acceptance and psychological flexibility with the idea of improving catastrophizing, kinesiophobia, anxiety, depression, quality of life, and overall personal functioning of people with chronic pain both before and after surgery, as measured by the degree of pain interference (primary endpoint of our study).

Predicting the prognosis in patients scheduled for surgery for LBP, through previous evaluation tests, could be efficient to apply them to complementary treatment modalities and thus prevent the chronification of pain and the worsening of functionality. People with chronic degenerative LBP who are candidates for surgery, with higher rates of catastrophizing, anxiety, depression, and fear of movement (kinesiophobia) will present a higher risk of chronic pain and a worse prognosis in relation to the efficacy of surgical treatment. We posit that participants receiving ACT will have greater improvement in pain intensity, pain interference, and quality of life, and less disability than participants receiving only TAU. It is hoped that ACT can improve the results in the variables studied in relation to chronic pain in this population with a high postsurgical risk of LBP.

Finally, we would like to mention that including TAU alongside an intervention in a clinical trial is not only important from a scientific perspective, but also from an ethical one. It is necessary to consider the patient’s perspective and ensure that they receive the appropriate treatment and the best possible care. In some cases, TAU may be the best available treatment for a given condition. In addition, this helps to prevent patients in the clinical trial from being subjected to unnecessary risk by receiving only the experimental intervention without having the standard treatment option.

Nevertheless, including TAU alongside an ACT in an RCT may introduce different types of biases that could affect the interpretation of the results. Confounding bias can make it difficult to separate the effects of treatment as usual from the effects of the experimental treatment. To minimize the biases that may arise when including TAU alongside an intervention in our RTC, we will carefully monitor variables that could explain the study results, such as patient characteristics (medical history, comorbidities, and medication) and intervention characteristics (adherence to treatment as usual, dropouts, administration format, therapist experience, and patient expectations). Monitoring these variables (which are collected in the RCT battery of measures) can help us to improve the validity of the study results.

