There is a growing understanding of the important role that psychological interventions can play in reducing negative affect, avoidance behaviors, and pain perception after surgery. Specifically, ACT allows patients to learn to expand their ability to experience and accept pain, including the negative thoughts and feelings that inevitably arise when pain is present. Physical pain sensations, as well as patient psychological reactions to them, are observed in a neutral, non-reactive manner, while focusing on improving motivation and commitment to engage in personally meaningful, achievable, and goal-oriented activities. This is practiced without engaging in problematic avoidance behaviors, which typically worsen pain and limit functioning. Patients become more psychologically flexible and learn to adapt their behavior in a way that allows them to live a rich and meaningful life [37]. Finally, previous studies have shown that psychological predictors have a significant association with the development of CPSP. Kinesiophobia and depression are independently associated with chronic postsurgical pain and disability and decreased physical function after lumbar spine surgery [38,39,40,41,42,43,44].

The present work describes the design of a randomized controlled trial (RCT) comparing the effectiveness of preoperative ACT versus treatment as usual (TAU) to improve pain interference in patients subjected to surgery for degenerative lumbar pathology. Considering the above evidence, we hypothesize that participants who engage in ACT will have greater improvement in quality of life and less disability and pain interference compared to participants who do not engage in ACT. The objectives of this RCT are the following: (a) to analyze the effectiveness of ACT as an adjuvant to TAU to improve pain interference (primary outcome); (b) to examine the effectiveness of ACT for improving pain intensity, anxiety, depression, pain intensity, quality of life, functional status, kinesiophobia, pain catastrophizing, psychological flexibility, and pain acceptance (secondary outcomes); and (c) to explore the differences between responders and non-responders in terms of sociodemographic and clinical characteristics.

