To determine the clinical significance of improvements on the primary outcome (BPI), patients will be classified into two categories: responders and non-responders. Considering the Initiative on Methods, Measurement, and Pain Assessment in Clinical Trials (IMMPACT) recommendations, a 1-point reduction in the pre–post and pre-follow-up BPI total score are used as a criterion for establishing clinically significant improvement [78]. This categorization was also used to calculate the number needed to treat (NNT) in TAU + ACT compared to TAU, with a 95% confidence interval (CI) calculated for each NNT at post-treatment and at follow-up. Furthermore, between-group differences in sociodemographic and clinical characteristics, and outcomes at baseline, post-treatment, and follow-up will be examined for responders versus non-responders using the Chi-Square test or Fisher’s exact test and Student’s *t*-tests for categorical and continuous variables, respectively.

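### The one subgroup analysis described omits the TAU arm, and the responder comparison includes the BPI scores that define response

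*Protocol article*

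**What the plan says.** Two stated analyses are involved.

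- **Stratification by risk factor (section 3, Discussion).** The article states: "we will stratify the patients who have undergone ACT based on the number and type of psychological factors of CPSP presented". The aim given is to see whether there are significant differences. No TAU comparator and no interaction term is named. Elsewhere in the Discussion, patients with higher levels of these same factors "will present a higher risk of chronic pain and a worse prognosis in relation to the efficacy of surgical treatment".
- **Responder comparison (section 2.6).** The definition is: "a 1-point reduction in the pre–post and pre-follow-up BPI total score are used as a criterion for establishing clinically significant improvement". Then, besides sociodemographic and clinical characteristics, "outcomes at baseline, post-treatment, and follow-up will be examined for responders versus non-responders", using t-tests for continuous variables. Table 2 lists BPI interference and BPI intensity among the outcomes at every visit. The section does not say whether the arms are pooled.

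Three other statements bear on the point. Objective (c) in the Introduction is narrower than section 2.6: "to explore the differences between responders and non-responders in terms of sociodemographic and clinical characteristics". The Discussion also says of the trial as a whole that "we will seek to recognize relevant moderators and mediators of clinical change", without a method. And responder status is used in a randomised contrast, to "calculate the number needed to treat (NNT) in TAU + ACT compared to TAU".

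**The concern.** A difference between ACT patients with many and with few risk factors may simply be the difference that would be seen under TAU. Because the article expects these factors to worsen outcome after surgery, the ACT-only contrast should be expected to differ even if ACT works equally well in everyone. A randomised control arm with the same instruments at the same visits is available and is not used.

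The responder comparison has a different fault. Patients are split on the change in a score and then tested on the two scores that make up the change. Responders must on average start higher and end lower, through regression to the mean and selection, with or without a treatment effect. The part on baseline characteristics is not circular, but it contains no treatment-by-factor term. It can show who improved, not who improved because of ACT, and every patient is a surgical candidate who may improve in either arm.

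At stake is the reading of secondary, exploratory results: a significant test in either analysis could be taken as information about ACT when it is not.

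**Working it through.** The article gives no figure for these analyses, so there is none to reproduce. From section 2.2 come 51 patients per arm and 30% dropout, hence 51 x 0.7 = 35.7, about 36 completers per arm. The effect of 0.64 SD is the article's post-treatment planning value. All SDs, correlations, prognostic effects and split proportions below are assumptions, because the article states none.

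**1. ACT-only contrast against a two-arm interaction**

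Set-up: ACT effect 0.64 SD in everyone (no true modification), factor split 50:50, the same prognostic effect g in both arms, two-sided 5%, 20,000 simulated trials per setting.

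| g (SD) | Within-ACT test, 36 per arm | Within-ACT test, 51 per arm | Two-arm interaction |
|---|---|---|---|
| 0 | 5% | 5% | about 5% |
| 0.3 | 14% | 18% | about 5% |
| 0.5 | 30% | 42% | about 5% |
| 0.8 | 65% | 80% | about 5% |

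Check by formula at g = 0.5: the noncentrality is 0.5 x sqrt(m/2) with m patients per subgroup. For m = 18 it is 1.50 and power is 0.31; for m = 25.5 it is 1.79 and power is 0.42. With a quarter of patients in one stratum the simulated rates at g = 0.5 are 24% and 33%.

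**2. Gap in BPI forced by the responder definition**

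Let baseline and follow-up BPI have common SD s and correlation r, and let response be a fall of at least 1 point. The change has SD s x sqrt(2(1-r)), and its correlation with baseline is -sqrt((1-r)/2). With no treatment effect and no mean change, t = -1 / (s x sqrt(2(1-r))), and the gap between responders and non-responders in baseline BPI, in SD units, is

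[phi(t)/Phi(t) + phi(t)/(1 - Phi(t))] x sqrt((1-r)/2).

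The follow-up gap has the same size and the opposite sign.

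For s = 2.2 and r = 0.5: the SD of change is 2.2, t = -0.455, phi = 0.360, Phi = 0.325. The bracket is 1.108 + 0.533 = 1.641, and 1.641 x 0.5 = 0.82 SD, or 1.8 points.

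| r | Gap, no mean change | Gap, mean fall of 1 point in everyone |
|---|---|---|
| 0.4 | 0.89 SD | 0.87 SD |
| 0.5 | 0.82 SD | 0.80 SD |
| 0.7 | 0.65 SD | 0.62 SD |

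The gap therefore hardly depends on the assumption of no mean change. A simulation with no ACT effect, a mean fall of 1 point, 72 completers pooled, SD 1.8-2.6 and r 0.3-0.7 (2,000 trials per setting) gave a significant baseline BPI difference in 76-99% of trials, with responders 1.1 to 2.5 points higher. The follow-up difference was significant in 77-99%, with responders 1.1 to 2.5 points lower.

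**3. Power of the valid contrast**

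For four cells of n/2 patients, the standard error of the interaction is sqrt(4/(n/2)): 0.471 SD for n = 36 and 0.396 SD for n = 51. Power is Phi(d/SE - 1.96). For d = 0.64 this is Phi(-0.60) = 27% and Phi(-0.34) = 37%. For d = 0.32 it is 10% and 13%; for d = 1.0 it is 56% and 71%.

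**The case against.** Several stronger readings are tempting, and the article does not support them.

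- **That effect modification will be judged in the ACT arm only.** A reader might join the stratification sentence to the moderator aim. That aim is a separate statement about the whole trial, not confined to one arm. Its method may sit in a fuller protocol or analysis plan that is not shown, so the lack of a method there is not a fault.
- **That the article claims these analyses show who benefits from ACT, or will use them to select patients.** Neither passage says so. Objective (c) is worded as exploration.
- **That responders are compared only on what defines them.** Most of the outcomes in Table 2 (HADS, PCS, TSK-11, CPAQ, PIPS, SF-12, Oswestry) do not define response. Only the BPI is tied to the definition by construction. The criterion names the BPI total score, so the calculated gap applies to that score; interference and intensity are affected as its parts.
- **That the stratification selects on treatment uptake.** The words can be read that way, but section 2.6 applies intention to treat to all analyses, and the sentence may simply mean the ACT arm.

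It is also fair to say that the sizes rest on assumed inputs, that the replacement test is weak, and that no confirmatory result is touched. These objections limit the point's scope and weight. They do not rescue the two analyses as written: an ACT-only contrast still lacks its comparator, and the BPI comparison is still circular. Both are stated choices, not details left for later.

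**Conclusion.** The point holds in a limited form. The ACT-only stratification cannot tell prognosis from modification of the ACT effect. For a purely prognostic factor of 0.5 SD split in half, it gives a significant result in about 30-42% of trials, and in 14-80% as the assumed effect runs from 0.3 to 0.8 SD. The BPI part of the responder comparison yields a gap of about 0.65-0.9 SD in each direction by definition alone, given an SD of 2.2, r of 0.4-0.7 and no mean change, and it goes beyond objective (c). The direction of both faults follows from the design of the analyses; only their size depends on the assumptions. The primary mixed model and the randomised NNT comparison stand, so this is a minor correction at the exploratory level.

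**What to change.** - **Discussion, stratification sentence.** Replace the ACT-only comparison with arm-by-baseline-factor interactions in the planned linear mixed model, fitted to all randomised patients. Use the number of risk factors and the continuous baseline HADS, PCS and TSK-11 scores. Report the estimates with confidence intervals and label them exploratory. Section 2.6 keeps baseline characteristics out of the outcome models as covariates, so say that these are separate exploratory models; each needs the main effect of its factor.
- **Section 2.6, responder comparison.** Remove the BPI at baseline, post-treatment and follow-up. Limit the comparison to baseline characteristics, in line with objective (c), and describe it as showing who improved, not who improved because of ACT. Leave the NNT as it is.

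The cost is a change of wording; Table 2 already provides the data in both arms. The drawback is low power, about 27-37% for an interaction as large as 0.64 SD, so a non-significant interaction must not be read as evidence that the effect is uniform.
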